## Interventions

### Usual care group

The usual care group (*n* = 50) will receive the usual care offered to participants who complete the 12-week Strength2Strength program. Follow up surveys are sent to participants at 3, 6 and 12 months’ post program to determine their current level of self-reported physical activity and sitting time (Fig. 2). Participants are also asked if they feel their activity levels have increased, decreased or stayed the same, reasons for a decrease in activity levels and how confident and motivated they are to continue to be physically active. Participants will attend assessments at 3, 6 and 12 months’ post program completion for collection of physiological variables, functional testing, physical activity and quality of life questionnaires, and health services usage data.

**Fig. 2 Fig2:**
[figure not shown]
Usual Care Follow Up Questionnaire administered at 3, 6 and 12 months’ post program

### Remote physical activity monitoring

Participants randomised to the remote physical activity monitoring group (*n* = 50) will receive a Jawbone activity tracker at the end of the 12 week S2S program. They will be requested to wear the Jawbone on their wrist, or ankle if the wrist is not a suitable option, for the duration of the 12 month follow up period. The activity tracker will be set up to provide feedback, via vibrotactile alert, to participants on their compliance to their individual prescribed activity levels (50 & 100% of prescribed daily activity). These levels will be prescribed by the exercise physiologists as part of the S2S program. In addition to the feedback achieved while wearing the device, participants will be requested to synchronise their Jawbone device to the study database at the end of each day using a mobile internet link they will be provided with as part of the study. The daily synchronisation will also serve to recharge the Jawbone device for the following day’s use. In the event that a participant fails to synchronise the device at the end of the day they will be sent an automated text message reminding them of the need to recharge their device regularly and the synchronisation and recharge will occur when they next connect. As part of the daily synchronisation participants will receive further feedback regarding their overall progress during the intervention. This will include feedback regarding progress towards daily and weekly physical activity targets, general health tips and remote feedback from the Exercise Physiologists regarding ongoing compliance to the individualised exercise program. Participants will attend assessments at 3, 6 and 12 months post program completion for collection of physiological variables, functional testing, physical activity and quality of life questionnaires, and health services usage data.

### Telephone counselling

Following the completion of the 12-week Strength2Strength program, participants (*n* = 50) will receive a follow up phone call once a fortnight for the first 3 months of the follow up period, and once a month for the remaining 9 months of the follow up period from the Exercise Physiologists. Participants will be asked to self-report on how they feel they are going with their activity levels and compliance to the home based program and if there are any issues that they feel are preventing them from being more physically active (Fig. 3). Participants will be provided assistance for any specific issues reported. Participants will attend assessments at 3, 6 and 12 months post program completion for collection of physiological variables, functional testing, physical activity and quality of life questionnaires, and health services usage data.

**Fig. 3 Fig3:**
[figure not shown]
Telephone consultation recording sheet

### Outcome measures

Outcome data pertaining to physical function, quality of life, physical activity levels, and markers of clinical prognosis (BMI, waist circumference, brachial blood pressure) will be collected at the start and end of the 12 week S2S program and again at 3, 6 and 12 months of follow up after the participants have been randomised to one of the 3 interventions. All outcome measures will be collected for all three treatment groups at all time-points.

### Physical activity measurement

Physical activity will be measured using two tools (a physical activity tracker and a questionnaire). Physical activity will be measured for a period of seven days at each time point through the use of ActivPal activity trackers. These will be fitted and worn day and night for the entire seven-day period with a minimum of five days’ worth of valid data required for inclusion at each assessment time. These trackers are reliable and valid [16, 17] for physical activity monitoring. Data obtained from the ActivPal activity trackers will be the primary measure of physical activity and expected changes to data obtained from these trackers form the basis of the sample size calculation for this study.

The physical activity questionnaire that will be used is the Active Australia questionnaire [18]. It will be included as a back-up activity monitor and to assess changes in time spent in different types of activities. Participants will be requested to include any exercise performed in the previous week in their response to the questionnaire. The survey measures frequency, intensity and duration of incidental and/or intentional physical activity in the week prior to the time of testing. The total time spent in each activity will be multiplied by an intensity value and used to calculate participants’ weekly physical activity in MET.min^−1^. This survey is valid and reliable [19, 20] and has previously been used to measure changes in physical activity in chronic disease populations [21].

### Motivation for exercise

The self-regulation Questionnaire for exercise (SRQ-E) is a theoretically derived questionnaire developed for use in school settings but which has since been validated in diverse health settings [22]. The SRQ-E gathers information on why a person chooses to exercise regularly and assesses the degree to which individuals are autonomous in exercise behaviour.

### Self-reported physical function (quality of life)

Self-perceived physical function will be evaluated using the Medical Outcomes Short-Form 36-Item Health Survey (SF-36). This survey includes 8 independent scales and assesses physical and mental dimensions of health. It is validated and has been widely used to measure quality of life in a range of chronic disease populations [21, 23, 24].

### Physical function

The six-minute walk test (6MWT) or Modified Shuttle Walk Test (MSWT) will be used as the measure of physical function. Both tests require minimal equipment and are quick and easy to conduct. The 6MWT requires participants to walk as far as possible along a short measured course during the six minutes. They will be permitted to stop and rest if needed and will receive regular encouragement throughout the test. The MSWT is an incremental walk test requiring participants to walk along a short measured course while keeping pace with a recording. Both the 6MWT [25] and MSWT [26] are reliable and valid measures of physical function in patients with metabolic disease.

### Muscle strength

Strength will be measured using the ten times sit to stand (TTSTS). TTSTS is a functional lower body strength measure that relates to ability to perform activities of daily living and consequently is relevant to wider health and quality of life outcomes. It is a reliable and valid measure that is widely used in clinical practice [27].

### Dynamic balance and mobility

Dynamic balance and mobility will be measured using the timed up and go (TUG). This test involves the client standing up from an armless chair and walking around a cone placed 2.44 m in front of the chair, returning to the chair and sitting down. It is a reliable and valid measure of dynamic balance and is widely used in clinical practice [28].

### Body composition

Three indicators of body composition will be measured. These are body mass index, waist circumference and percent body fat. These measures are simple and easy to attain and have been widely used as indicators of cardiovascular disease (CVD) [29] and mortality [30] risk in large scale population studies. Body Mass Index (BMI) will be calculated from height and body weight. Waist circumference will be measured at the narrowest point between the base of the rib cage and the iliac crest as per standard methods. Body fat percent will be assessed through the use of Bio-Impedance Analysis scales (Tanita BC-1000; Tanita Corp; Tokyo, Japan). BIA has previously been shown to be a reliable and reproducible method for determining body composition [31, 32].

### Blood pressure

Brachial blood pressure will be measured by sphygmomanometry using standardised techniques after five minutes of seated rest.

### Health Service Usage

Retrospective (covering before and during the study) information about medications (Medical Benefits Scheme (MBS) and Pharmaceutical Benefits Scheme (PBS) items of service from the Australian Department of Human Services, hospitalisations (Department of Health and Human Services Clinical Costing Dataset [electronic inpatient separation summary] for costing’s and morbidity) and mortality (AIHW National Death Register) will be collected. Out-of-pocket expenses, incidental and non-billable health professional encounters, and work missed through ill health will be assessed by health diaries to be maintained by each patient over the intervention and follow up periods (Fig. 4).

**Fig. 4 Fig4:**
[figure not shown]
Example Health Service Usage Diary entry

### Adherence to the intervention

Participant adherence to the treatment interventions will be assessed through records of the proportion of intervention days that participants randomised to the remote physical activity monitoring group wear their activity monitor. Records will also be kept and reported regarding the the proportion of telephone calls successfully delivered to participants in the telephone counselling group as well as the length and content of these calls.

### Sample size calculation

The 12 week S2S intervention resulted in a mean increase of 450 MET.min of physical activity per week with a SD of 1.5x the change. Sample size was calculated based on a predicted maintenance of 100% of additional physical activity in the feedback groups and decrease of 50% of additional physical activity in the usual care group over the 12-month intervention (Mean Difference = 225 Met.min/week) with a SD of the change of 350 MET.min/week (1.5x the mean change in line with S2S data). STATA 12 (Statistical data analysis; Stata Corp; College Station; Texas, USA) was used to calculate the sample size on the basis of a mean difference of 225 MET.min/week with a SD of the change of 350 MET.min/week, a power of 80% and an alpha level of 0.05 using the “sampsi 0 225, sd (350) p (0.8) a (0.05)” command. The sample size calculation indicated that at least 38 participants were required per group. To allow for potential withdrawals 50 participants per group will be recruited.

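### The planning SD of 350 MET.min/week is about half the 675 that the cited S2S data imply; on the S2S figure, 38 per group gives about 31% power rather than 80%

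*Protocol article*

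**What the plan says.** All of the reasoning for the sample size is in one paragraph of the protocol article, under Sample size calculation. It opens with the earlier experience of the program: "The 12 week S2S intervention resulted in a mean increase of 450 MET.min of physical activity per week with a SD of 1.5x the change". It then assumes that the feedback groups keep all of that gain over 12 months and the usual care group loses half, which gives "Mean Difference = 225 Met.min/week". The SD is entered as "with a SD of the change of 350 MET.min/week (1.5x the mean change in line with S2S data"). The Stata command is "sampsi 0 225, sd (350) p (0.8) a (0.05"), and the criteria are "a power of 80% and an alpha level of 0.05". The result is given as: "The sample size calculation indicated that at least 38 participants were required per group". Recruitment is set at 50 per group to allow for withdrawals.

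The Physical activity measurement section says that this calculation rests on expected changes in the ActivPal data, the primary measure of physical activity.

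**The concern.** The paragraph contains one S2S mean change, 450, and one S2S ratio of SD to mean change, 1.5. Together they give an SD of 675. The planning value of 350 is described as following the same rule, but it matches the rule only when the ratio is applied to 225, the targeted difference between arms.

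That step has no basis. The SD in a two-sample calculation describes how much individual changes vary within an arm, and halving the difference to be detected does not halve that variation. Applied as written, the rule also contradicts itself. The command sets the mean change in the feedback groups to 0, so the rule would give those groups an SD of 0, yet 350 is used for both groups.

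This calculation is the only justification for 38 evaluable and 50 recruited per group. If the true SD is near the S2S value, a real difference of 225 MET.min/week would more often be missed than found. A reader relying on the stated 80% could then take a non-significant result as evidence that ongoing feedback does nothing.

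**Working it through.** **Inputs, all from Sample size calculation**

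- S2S mean change: 450 MET.min/week
- S2S SD of change: 1.5 × 450 = 675 MET.min/week
- Difference to detect: 225 MET.min/week (50% of 450)
- SD entered: 350 MET.min/week (1.5 × 225 = 337.5, apparently rounded up)
- Alpha 0.05 and power 80%. Sidedness is not stated in words. Two-sided reproduces the published 38 and one-sided gives 30, so two-sided is used.

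**Formulas (normal approximation, equal groups)**

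- n per group = 2 × (1.960 + 0.842)² × SD² / 225²
- power = Φ(225 / (SD × √(2/n)) − 1.960)
- detectable difference at 80% power = 2.802 × SD × √(2/n)

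**Step 1. The plan's own figure.** With SD 350, n = 2 × 2.802² × 350² / 225² = 37.98, rounded up to 38. The command is computed correctly; the fault is in the SD it was given. With the unrounded 337.5, n would be 36.

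**Step 2. The S2S SD.** With SD 675:

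- n = 2 × 2.802² × (675/225)² = 141.3, so 142 per group
- power at 38 = Φ(225 / (675 × √(2/38)) − 1.960) = Φ(1.453 − 1.960) = 30.6%
- power at 50, no withdrawals = Φ(225 / (675 × √(2/50)) − 1.960) = Φ(1.667 − 1.960) = 38.5%
- detectable difference = 434 MET.min/week at 38 per group and 378 at 50

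The t-test versions are almost the same: 30.0% at 38, 37.9% at 50, and 143 per group for 80%. The standardised effect falls from 225/350 = 0.64 to 225/675 = 0.33.

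**Step 3. Sensitivity to the SD**

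| SD (MET.min/week) | Power at 38 | Power at 50 | n per group for 80% |
|---|---|---|---|
| 350 | 80% | 90% | 38 |
| 400 | 69% | 80% | 50 |
| 450 | 59% | 71% | 63 |
| 500 | 50% | 61% | 78 |
| 600 | 37% | 47% | 112 |
| 675 | 31% | 38% | 142 |

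**Step 4. The most generous reading of the proportional rule.** Suppose the SD does scale with the mean change, and change is measured from before S2S. The predicted gains are then 450 with feedback and 225 with usual care, with SDs of 675 and 337.5. Their root mean square is √((675² + 337.5²)/2) = 534. Power is about 45% at 38 per group and 56% at 50, and 89 per group would be needed. This reading does not yield 350 in both arms either.

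**The case against.** The strongest reply is that 675 is not known to be the right value. It describes change during a supervised 12-week program, whereas the trial compares change over 12 months of follow-up. The instrument is also uncertain. The Physical activity measurement section ties the calculation to ActivPal data but mentions MET minutes only for the Active Australia questionnaire, and the article does not say which tool produced the 450. This stands, and it makes the 31% conditional on the S2S SD carrying over. It does not support 350, because S2S is the only evidence the paragraph cites and the paragraph claims to agree with it.

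A second point is that 50 per group are recruited and Data analysis carries the last value forward, so the number analysed may be close to 50. Power is then about 38%, still under half the target, and values carried forward may themselves dilute the effect.

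A third is that the planned analysis is a mixed model over repeated assessments, not a two-sample comparison of one change score. It may recover some precision. To bring 675 down to an effective 350, it would have to remove 1 − (350/675)² = 73% of the variance, equivalent to a correlation of about 0.86. The protocol claims no such gain.

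Finally, nothing was miscalculated in the command itself. That is true; what is wrong is the SD fed into it and the claim about where it came from.

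**Conclusion.** The concern holds. The planning SD is about half the value implied by the S2S figures in the same paragraph (350/675 = 0.52), and the statement that it agrees with those data is wrong. On the document's own figures, power for a difference of 225 MET.min/week is about 31% with 38 evaluable per group and 38% with all 50 retained, against the stated 80%. The trial could detect with 80% power only a difference of 434 (38 per group) or 378 (50 per group), close to the whole 450 gained during S2S.

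These figures assume a two-sided 5% test, an unadjusted comparison of two groups, and an SD of 12-month change equal to the S2S SD. The conclusion does not need 675 exactly. Among the SDs above 350 in the table, only 400 reaches 80%, and only if all 50 per group are retained.

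**What to change.** In Sample size calculation:

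1. Replace 350 with 675, or with an observed SD of 12-month change, giving its source and the instrument it was measured with.
2. Remove the statement that 350 agrees with the S2S data.
3. Restate the power and the detectable difference for 38 evaluable and 50 randomised per group. With SD 675 these are 31% and 434 MET.min/week at 38, and 38% and 378 MET.min/week at 50.
4. Keep the total at 150. Reaching 80% power with SD 675 would take 3 × 142 = 426 evaluable participants, before any allowance for withdrawals.
5. Recover what precision is available by adjusting the primary comparison for baseline physical activity, and commit to interpreting the primary result by its confidence interval, so that a non-significant result is not read as no effect.

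The cost is the rewording of one paragraph and a less favourable stated power. No participants are added.

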## Data analysis

All statistical analyses will be performed using STATA statistical software (STATA 13; Statistical data analysis; Stata Corp; College Station; Texas, USA). Baseline and descriptive data between the groups will be analysed with one-way ANOVA. Binary categorical data will be analysed for variability between the groups using logistic regression. Parametric longitudinal data will be analysed using mixed effects linear regression with unstructured covariance, corrected for repeated measures. In the event that assumptions of linear regression (heteroskedascity, skewness, kurtosis or non-linearity) are violated, those analyses will be repeated using repeated measures ordinal logistic regression. *P*-Values will be corrected where appropriate for multiple comparisons using the Holm test. Where participants do not return for follow up or there is missing data, this will be analysed on a last case brought forward basis.

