### Selection of participants

Inclusion Criteria are individuals referred to the Strength2Strength (S2S) Tasmania Exercise Treatment Initiative. The S2S Tasmania Exercise Treatment Initiative is an individually tailored 12-week exercise lifestyle program that is led by Accredited Exercise Physiologists and targeted at individuals who are:elderly, frail and agedare at risk of developing chronic diseasehave a chronic medical condition including neurodegenerative disease, cardiovascular disease and conditions, chronic obstructive pulmonary disease (COPD), type 2 diabetes, muscular and/or skeletal conditions, mobility or gait issues and those receiving steroid treatment.

Due to some of the outcome variables from S2S being utilised in the research, participants will be recruited as they commence S2S. The proposed research will investigate the ongoing engagement of S2S participants once they have exited that program. Some of the outcome variables from the S2S program will be utilised in the proposed research but only for those participants who consent to participate in the research study. The reason for use of these outcome variables is to inform of changes in health and physical activity status that occurred during S2S as these changes may impact on how physical activity levels and health outcomes change during the follow up (intervention) period. Data will be collected from S2S site in Launceston, Tasmania, Australia only.

Exclusion criteria: Individuals who choose not to participate in the S2S program will not be considered. Anyone presenting with an unstable medical condition preventing them from participating in regular physical activity; or individuals with neurological conditions, or limited understanding of English which prevent them from meeting the self-reporting requirements of the study will also be excluded.

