### Randomisation

Participants who enrol in the study will undergo baseline testing and the 12 week S2S program before being randomised to one of the three intervention groups. Randomisation of participants to intervention groups will be performed at the end of the S2S endpoint testing session. Randomisation will be performed using computer generated blocks of fifteen by a third person not directly involved in the study and will be recorded in sealed opaque envelopes. Each envelope will be opened sequentially at the endpoint S2S endpoint testing session to reveal the allocated intervention. In the event that there are multiple participants from the same household they will be randomised to the same group to maintain the integrity of the intervention. All participants will be requested to avoid the use of any physical monitoring devices other than those directly provided by the researchers for the duration of the study.

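### The end-of-S2S activity value has no stated role as an adjusting baseline, and its seven-day recording is not protected from falling after allocation

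*Protocol article*

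**What the plan says.** **Analysis.** The Data analysis section of the protocol article states that "Baseline and descriptive data between the groups will be analysed with one-way ANOVA", and then that "Parametric longitudinal data will be analysed using mixed effects linear regression with unstructured covariance, corrected for repeated measures". It names no baseline covariate, reference time point or arm-by-time contrast. Missing values are to be carried forward.

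**Meaning of baseline.** Under Randomisation, "Participants who enrol in the study will undergo baseline testing and the 12 week S2S program before being randomised"; baseline there is the test before S2S. The Objectives, however, concern maintenance after S2S, and the Sample size calculation uses the SD of the change over the 12-month follow-up, so both start from the end-of-S2S value. Selection of participants gives the reason for using S2S-period data: "these changes may impact on how physical activity levels and health outcomes change during the follow up (intervention) period". No role in the model follows from this.

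**Timing.** "Randomisation of participants to intervention groups will be performed at the end of the S2S endpoint testing session", and "Each envelope will be opened sequentially at the endpoint S2S endpoint testing session to reveal the allocated intervention". The remote-monitoring group "will receive a Jawbone activity tracker at the end of the 12 week S2S program". Under Physical activity measurement, the ActivPal is the primary measure at every time point. On wear, "These will be fitted and worn day and night for the entire seven-day period", with at least five valid days required.

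**The concern.** Two things are at stake, and they differ in kind.

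The first is precision. The end-of-S2S value is to be collected in all three arms and is likely to predict later activity. A test of whether randomised arms differ on a pre-allocation value examines a null hypothesis already known to be true, and does nothing with that information. Adjustment uses it. Leaving it out does not bias a randomised comparison, but it widens the interval.

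The second is bias, and it is conditional. A seven-day record cannot be completed within one session. If the ActivPal goes on at the session where allocation is revealed and the feedback tracker handed over, the reference week is an unblinded post-allocation measurement. Any early response to the tracker would then sit in the reference value and be subtracted, wholly or partly, from the effect. The five-valid-day rule could also come to depend on arm.

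**Working it through.** **1. The plan's own figure.** Inputs from the Sample size calculation: difference 225 MET.min/week, SD of the change 350, alpha 0.05, power 80%. Two-sided:

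n = 2 × [350 × (1.960 + 0.842) / 225]² = 37.98, so 38 per group. The stated figure reproduces. On the same inputs, 50 per group gives about 90% power before withdrawals.

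**2. What an unconstrained model estimates.** With values carried forward, every participant has a value at each follow-up. With complete data and a free mean for each arm at each time, the model returns the observed means whatever the covariance. The arm difference in change from end of S2S to 12 months is then simply the change-score difference, and the unstructured covariance does not recover the gain from adjustment.

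**3. Change score against adjustment.** Let rho be the correlation between the end-of-S2S and 12-month values, with equal variances s² at both times. The document gives no rho, so a range is shown.

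- Variance of a change: 2s²(1 − rho)
- Residual variance after adjustment: s²(1 − rho²)
- Ratio: (1 + rho)/2

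The adjusted SD is therefore 350 × √[(1 + rho)/2], and the n needed is 37.98 × (1 + rho)/2, rounded up.

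| rho (assumed) | Variance ratio | Adjusted SD | n per group | Power at 38 |
|---|---|---|---|---|
| 0.2 | 0.60 | 271.1 | 23 | 95% |
| 0.5 | 0.75 | 303.1 | 29 | 90% |
| 0.7 | 0.85 | 322.7 | 33 | 86% |
| 0.8 | 0.90 | 332.0 | 35 | 84% |

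The comparator throughout is the change score: 38 per group, 80% power.

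**4. A reference week recorded after allocation.** Suppose a fraction f of the 225 effect is already present in that week, so d = 225f. The document gives no f. The change-score estimate becomes 225(1 − f), a bias of −d. The adjusted estimate becomes 225(1 − rho × f), a bias of −rho × d. Power is Φ[Δ / (SD × √(2/n)) − 1.96], where Δ is the attenuated effect.

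| f (assumed) | Change-score effect | Power at 38 | Power at 50 | Adjusted effect, rho 0.5 | Adjusted effect, rho 0.7 |
|---|---|---|---|---|---|
| 0 | 225 | 80% | 90% | 225 | 225 |
| 0.10 | 202.5 | 71% | 83% | 213.8 | 209.2 |
| 0.25 | 168.75 | 56% | 67% | 196.9 | 185.6 |
| 0.50 | 112.5 | 29% | 36% | 168.8 | 146.2 |

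Adjustment lessens this bias but does not remove it. Only the order of recording and allocation does.

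**The case against.** **On adjustment.** A reader might infer that the end-of-S2S value is merely tested by ANOVA and otherwise unused. The text does not say that. The Outcome measures section lists end of S2S among the collection times, and the mixed model may carry it as a repeated outcome. Since baseline under Randomisation means the pre-S2S test, the ANOVA sentence may not even refer to the end-of-S2S value. The exact model specification is also something an article can leave to an analysis plan, and nothing makes the model depend on the ANOVA results. All of this stands. What remains is that baseline testing is a stated choice with no use, and that a repeated outcome without a constraint yields only the change-score contrast.

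A reader might also infer that the trial is underpowered on this account. It is not shown to be: 38 reproduces and 50 are recruited. Whether 350 is a fair SD is a separate question.

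**On timing.** A reader might infer that the reference week does fall after allocation. No section says when the ActivPal is fitted. Randomisation comes at the end of the testing session, Outcome measures describes only the 3, 6 and 12 month data as collected after randomisation, and Fig. 1 is not available here. These point to an intention to measure first. The Active Australia questionnaire, which asks about the preceding week, would be free of the problem if completed at that session, but the article makes it the back-up measure. So the intention is plausible, but no stated step secures it.

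**On consistency.** If the end-of-S2S value were ignored in the model, its contamination could not bias the follow-up contrasts, so it may seem that both harms cannot apply. Under a change-score contrast they do both apply. Carrying values forward also makes the end-of-S2S value the outcome for anyone lost before 3 months.

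**Conclusion.** The point holds in two limited parts.

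First, the ANOVA baseline tests serve no purpose, and the stated model leaves the reference value without a covariate or constrained role. If it is used only as an unconstrained repeated outcome, the cost is precision, not validity: adjustment would reduce variance by 25% at rho 0.5 or 15% at rho 0.7. This rests on an assumed rho and on equal variances at the two times.

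Second, the sequence of endpoint session, envelope, Jawbone and seven-day recording does not guarantee a pre-allocation reference for the primary measure. Should the recording follow allocation, the remote-monitoring effect would be biased by −d or about −rho × d, towards zero if the tracker raises activity in the first week. Both the occurrence and the size of d are unknown, so the power figures in the second table illustrate the risk and do not estimate it.

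**What to change.** - **Data analysis:** remove the ANOVA tests of baseline data and describe the arms with summary statistics instead. Name the end-of-S2S value as the reference. Either enter it as a covariate in the mixed model, optionally with the pre-S2S value, or constrain arm means to be equal at end of S2S. Report arm differences at 3, 6 and 12 months. The constraint is justified by randomisation only if the value is recorded before allocation, so this change depends on the next one.
- **Randomisation and Physical activity measurement:** state that the seven-day end-of-S2S ActivPal record must be complete before the envelope is opened and the feedback tracker issued. Use distinct terms for the pre-S2S and end-of-S2S tests.

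**Cost:** model wording, and fitting the ActivPal about a week earlier while participants still attend S2S. The trial was registered retrospectively and recruitment may already have begun. If so, apply the timing rule to later participants, and record which earlier reference records were made after allocation so that the mixture is visible in the analysis.
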